# TIME – Targeted interdisciplinary model for evaluation and treatment of neuropsychiatric symptoms: protocol for an effectiveness-implementation cluster randomized hybrid trial

**DOI:** 10.1186/s12888-016-0944-0

**Published:** 2016-07-12

**Keywords:** Dementia, Neuropsychiatric symptoms, Behavioural and psychological Symptoms of dementia (BPSD), Psychosocial interventions, Nursing home, Case conference

## Abstract

**Background:**

Nearly all persons with dementia will experience neuropsychiatric symptoms (NPS) during the course of their disease. Clinicians and researchers emphasize the need for an evidence-informed standardized approach to managing NPS that integrates pharmacological and nonpharmacological treatments for real-world implementation. The Targeted Interdisciplinary Model for Evaluation and Treatment of Neuropsychiatric Symptoms (TIME) represents such an approach and is a multicomponent intervention based on the theoretical framework of cognitive behavioural therapy.

**Methods/design:**

The trial is a 3-month cluster randomized trial conducted in 30 nursing homes including 168 participants with dementia and a high level of agitation. Each nursing home defined as a cluster will be randomized to receive either the TIME intervention (the intervention group) or a brief education-only intervention regarding dementia and NPS (the control group). TIME is a manual-based, multicomponent programme that includes a rigorous assessment, one or more case conferences and the treatment and evaluation of NPS. Patient-level measurements are taken at baseline (prior to randomization) and 8 and 12 weeks later. The primary outcome measure is the change in agitation, as defined by the Neuropsychiatric Inventory-Nursing Home Version, at 8 weeks from baseline. Secondary outcome measures include change in agitation at 12 weeks from baseline, and change from baseline at 8 and 12 weeks in other NPS, quality of life, and the use of psychotropic and analgesic medications. Mixed methods will be used to follow, measure and explore the implementation process and the effect of the intervention at the individual staff level and the organization level. Combining measurements of clinical effectiveness and implementation outcomes define this trial as an effectiveness-implementation hybrid trial.

**Discussion:**

Measuring the implementation and effect of complex interventions aimed at reducing NPS in nursing homes is challenging. In this study protocol, we describe a multicomponent program, TIME, and discuss how an effectiveness-implementation cluster randomized hybrid trial can meet these challenges.

**Trial registration:**

ClinicalTrials.gov identifier NCT02655003. Registered 6 January 2016.

## Background

In Norway, approximately 41,000 persons live in nursing homes, and more than 80 % of these have dementia [1, 2]. Nearly 70 % of persons with dementia in nursing homes exhibit clinically significant neuropsychiatric symptoms (NPS)—also labelled as behavioural and psychological symptoms of dementia (BPSD), such as psychosis, depression, anxiety, agitation and apathy [3]. NPS like agitation, including physical or verbal aggression and excessive motor activity cause patients to experience profound suffering and a reduced quality of life and caregivers to experience increased burden [4]. These symptoms represent great challenges in the care of nursing home patients and are predictors of referral to specialist health care and hospitalization [2, 5]. In a review article published in 2014, a multidisciplinary expert panel emphasized the need to develop comprehensive models for the assessment and treatment of these symptoms. Such models should enable the simple implementation of these recommendations in real-world settings [6].

A literature review by Livingstone et al. concluded that behavioural therapeutic techniques and psychoeducation aimed at altering the caregiver’s behaviour seemed to reduce NPS [7]. However, the findings regarding other types of treatment were inconclusive and inadequately documented. In a literature review that Testad et al. performed in 2014 on personalized interventions targeting NPS the authors noted increasing evidence that such interventions reduce NPS [8]. In a controlled trial, Cohen-Mansfield et al. showed that a systematic individual intervention based on a step-by-step algorithm significantly reduced agitation. Unfortunately, this study excluded patients exhibiting physical aggression, and the research team implemented the treatment measures in the wards [9]. Testad et al. conducted a randomized intervention trial in nursing homes in Norway and found that the systematic education and supervision of staff resulted in a reduced use of restraints although the level of agitated behaviour remained unchanged or increased slightly [10]. A systematic review by Reuther et al. including 432 studies of case conferences performed as interventions to address challenging behaviour concluded that four of seven studies in the analysis showed a reduction in the challenging behaviour of people with dementia [11]. The review highlighted the need for methodologically well-designed intervention studies. A disadvantage of many of these interventions is that they require a substantial amount of additional resources to nursing homes to be implemented successfully. A systematic review performed by Seitz et al. (2012) included 40 studies on various interventions aimed at reducing NPS. Sixteen studies showed positive results, but 75 % of them required a significant increase in the resources available to the nursing homes [12]. To our knowledge no trials have used principles from cognitive behavioural therapy (CBT) to structure care-delivery interventions to manage NPS in nursing homes.

### The development of the TIME intervention

The Targeted Interdisciplinary Model for Evaluation and Treatment of Neuropsychiatric Symptoms (TIME) was developed in nursing homes by the first author, BL. This model has been used in clinical practice in many nursing homes since it was first developed in 2007–2008. It requires minimal training, is manual based, and is easy to integrate into everyday clinical practice and care without major additional costs. The model is based on the theoretical frameworks of cognitive behavioural therapy (CBT) and person-centred care (PCC), which state that human behaviour is subject to the continuous influence of biological, social and psychological factors. Thus, the model integrates pharmacological and nonpharmacological treatments for real-world implementation. The primary purpose of the model is to allow an interdisciplinary team of staff and physicians to conduct a thorough assessment and critical systematic reflection in case conferences to achieve a mutual understanding of NPS and, thereby, implement customized actions based on this understanding. In 2010, The Centre for Old Age Psychiatric Research, Innlandet Hospital Trust conducted an open non-controlled trial in nine nursing homes over six months and included 30 persons with dementia and high levels of agitation. The results showed that patients’ agitation, mood symptoms and staff’s distress were significantly reduced. This study was published as an abstract in International Psychogeriatrics [13] and formed the basis for a revision of the TIME manual [14] and a web-accessible short film that can be used for training in the model [15]. In this abstract, the model was referred to as the Multidisciplinary Intervention Model for Challenging Behaviour in Nursing Home Patients with Dementia (MIND).

### Research aim and research questions

The primary purpose of this study is to improve the assessment and treatment of agitation in persons with dementia by examining the effect and implementation of the TIME intervention model. We formulated the following research questions: 1) Can an intervention utilizing TIME reduce agitation in persons with dementia in nursing homes? 2) Does TIME serve as a method of continuous learning and reflection? That is, can the model help develop and strengthen staff members’ confidence, mastery and competence at an individual level and at an organizational level? 3) What nursing home factors inhibit or promote the implementation of psychosocial intervention models such as TIME, and is implementation sustainable?

## Methods and design

### Study design

The first research question will be answered through a cluster randomized controlled trial with two parallel groups: Intervention Nursing Homes (INH) and Control Nursing Homes (CNH). Fig. 1 shows a flow chart of the clusters and individuals through the phases of the trial based on the power calculation. For the second and third research questions, we will utilise both quantitative and qualitative methods. Data will be gathered from the records of reflection meetings (case conferences) held during the trial, implementation checklists completed during the trial, four focus group interviews performed after the trial, and questionnaires administered before and after the trial. The trial is defined as an effectiveness-implementation cluster randomized hybrid trial because of the use of various types of data and the study design.

**Fig. 1 Fig1:**
[figure not shown]
The TIME trial: Flowchart of the clusters and individuals throughout the phases of the trial

### Settings and target population

Municipalities located in the north, middle and south-eastern part of Norway will be contacted to participate in the trial. To ensure collaboration and implementation throughout the trial, we will arrange meetings with the health care leaders in the municipalities and the managers and physicians working in each nursing home. We will strive to recruit nursing homes located in both rural and urban areas of Norway and to obtain an equal distribution of large and small nursing homes to ensure a representative nursing home population. Nursing homes already using TIME as part of their clinical routines will not be invited to take part in the trial.

All patients in wards in participating nursing homes will be considered eligible for inclusion in the trial, and will be assessed to determine if they meet the inclusion criteria. Trained nursing home staff will perform the assessments. The research team will train these staff members on the inclusion procedure and the assessment of patients’ capacity to provide consent. The data obtained from screening individual eligible patients will not be recorded. Patients who fulfil the inclusion criteria and agree to participate will be included in the trial. For patients who lack the capacity to provide consent, written consent will be obtained from their next of kin.

The inclusion criteria for patients are as follows:NH patients with probable dementia, defined as a Clinical Dementia Rating scale (CDR) [16] score of one or higher.A moderate to high degree of agitation, defined by an NPI-NH agitation item score equal to or above six points.Long-term patients who have resided in the nursing home for a minimum of two weeks before inclusion.

The exclusion criterion for patients is a life expectancy of less than 4–6 weeks.

### Sample size calculation based on the primary outcome

The primary outcome of the trial is the change in the level of agitation from baseline at eight weeks, as measured by the agitation item of the Neuropsychiatric Inventory-Nursing Home Version (NPI-NH) [17, 18]. Power calculation was based on the following assumptions. A previous non-controlled pilot study of TIME showed that the intervention decreased the NPI-NH agitation item score by on average 2.8, with a standard deviation (SD) for change of 3.1 [13]. One can reasonably assume that the simple education-only intervention and baseline and follow-up assessments may have some effect on the control group. Therefore, we expect that the difference in the effect between the control and intervention groups will be lower. We have assumed a mean difference between the groups to be 1.5 as measured by NPI-NH agitation item, and that this difference will have a SD of 3.1. Based on this assumption, we calculate that 65 persons must be included in each group to observe a statistically significant difference with a power of 80 % and a significance level of 5 %. We assume an intra-cluster (nursing home) correlation coefficient (ICC) of 0.05. The ICC is assumed to be low because the persons included will be located in different departments and units in the nursing home (the cluster). Adjusting power calculations for cluster effect, we find that at least 78 persons have to be included in the intervention group and 78 in the control group for the effect to be statistically significant. That is, we need a total of 156 persons. Based on previous studies, we assume that the average size of the nursing homes is 46 patients and that each nursing home will recruit five patients, on average. In the pilot study, we found that approximately 12 % of patients had dementia and an NPI-NH agitation item score of six or higher, which is our main criterion for inclusion. Previous studies have shown that we can anticipate a 30 % loss to follow-up per year (due to, e.g., mortality, relocation, or withdrawal from the study)—that is, 7.5 % in three months. Thus, we will need a total of 168 people (84 persons in each group), indicating that we will need to screen approximately 1400 nursing home patients. Given approximately 46 patients on average per nursing home, we will need to recruit approximately 30 nursing homes. The nursing homes will be randomized after the baseline assessment to avoid bias. The recruitment of new patients to the study will therefore occur only through the recruitment and randomization of new nursing homes, as described above.

This study must perform cluster randomization, with the nursing home as the cluster, for two main reasons. The TIME intervention is a biopsychosocial intervention that involves the entire interdisciplinary team and staff in the wards of the participating nursing homes to optimize the treatment provided to a group of patients in the wards. In addition, the study runs the risk of transmitting all or parts of the intervention model to the control units or individual control patients at the same nursing home [19].

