### Randomization

Nursing homes will be stratified by size into three blocks to assure approximately equal number of patients in the two trial arms. Block size will be fixed—block 1: 1–5 patients, block 2: 6–9 patients, and block 3: 10 or more patients. Then, nursing homes within each block will be randomly assigned to either the intervention group or the control group. A researcher will perform the randomization procedure independently of the project management team and the nursing homes. The project management team will provide the nursing homes with the randomization and allocation results immediately following this procedure. Specially trained project nurses who are not affiliated with the nursing homes will assess patients’ baseline characteristics before randomization. These assessors will also assess the effect of the intervention via telephone at weeks eight and 12 and will be blinded to the randomization result.

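### The base sample size of 65 per group should be 68 on the stated inputs; the error carries into 78, 156 and 168, and 168 patients give about 78% power rather than 80%

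*Protocol article*

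**What the plan says.** The section on sample size in the protocol article sets out the calculation in steps.

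- Effect: "We have assumed a mean difference between the groups to be 1.5 as measured by NPI-NH agitation item". The SD is set at 3.1, which equals the pilot study's SD for change.
- Error rates: "with a power of 80 % and a significance level of 5" per cent. Whether the test is one- or two-sided is not stated.
- Base size: "we calculate that 65 persons must be included in each group to observe a statistically significant difference".
- Clustering: "We assume an intra-cluster (nursing home) correlation coefficient (ICC) of 0.05", with an average of five patients recruited per home. This leads to "at least 78 persons have to be included in the intervention group and 78 in the control group", or 156 in total.
- Loss: 30% per year, taken as 7.5% over three months. "Thus, we will need a total of 168 people (84 persons in each group"), in approximately 30 nursing homes.

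The section on randomization stratifies homes by number of patients ("block 1: 1–5 patients, block 2: 6–9 patients, and block 3: 10 or more patients"), so homes of different sizes are expected. No measure of that variation is given.

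**The concern.** The base figure can be checked directly from four printed inputs, and it comes out too low. All later figures are multiples of it, and the last one, 168, is the enrolment target repeated in the abstract and the conclusion. If the base is wrong, the 80% power claimed for 168 patients is not what the stated assumptions deliver. The trial report is to follow the CONSORT extension for cluster trials, so the same calculation is likely to be reported again with the results.

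**Working it through.** **Inputs**, all from the sample size section: difference 1.5; SD 3.1; power 80%; significance level 5%, read as two-sided; ICC 0.05; five patients per home; loss 7.5%; 168 patients; 30 homes.

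**1. Base size.** n per group = 2 × (1.96 + 0.8416)² × 3.1² / 1.5² = 67.05, rounded up to 68. A two-sample t-test needs 68.02, that is 69.

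Other readings tried in order to reach 65:

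| Reading | n per group |
|---|---|
| One-sided 5%, normal / t | 53 / 54 |
| Standardised effect rounded to 0.5, normal / t | 63 / 64 |
| Standardised effect rounded to 0.48 | 69 |
| SD 3.05 in place of 3.1 | 65 |

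Only the last gives 65, and 3.05 is not the SD printed. With 65 per group and no clustering, power is 78.8% (normal) or 78.2% (t).

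**2. The plan's later steps, from its own base.**
- Design effect: 1 + (5 − 1) × 0.05 = 1.2.
- 65 × 1.2 = 78 per group, 156 in total. This reproduces.
- 156 × 1.075 = 167.7, that is 168. This reproduces.

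The later steps are therefore consistent with each other, and the fault lies in the base.

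**3. The same steps from the correct base.**
- Rounding up at each step: 68 × 1.2 = 81.6, so 82; 82 / 0.925 = 88.6, so 89 per group and 178 in total.
- Without intermediate rounding: 67.05 × 1.2 / 0.925 = 86.98 per group, about 174 in total.

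The stated total is short by 6 to 10 patients.

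**4. Power of 168 patients on the plan's own assumptions.**
- Analysed per arm: 84 × 0.925 = 77.7.
- Analysed per home: 168 × 0.925 / 30 = 5.18.
- Design effect: 1 + (5.18 − 1) × 0.05 = 1.209.
- Effective n per arm: 77.7 / 1.209 = 64.27.
- Standard error: 3.1 × √(2 / 64.27) = 0.547. Then 1.5 / 0.547 = 2.743, and power = Φ(2.743 − 1.960) = 78.3%.
- With a t reference on patient-level degrees of freedom: 77.8%.
- Difference detectable with 80% power (normal): 2.8016 × 0.547 = 1.53 points.

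**5. Sensitivity, separate from the error in 65.** The home is the unit of randomization, so a cluster-level test would have 30 − 2 = 28 degrees of freedom. Unequal homes raise the design effect to 1 + ((1 + CV²) × 5.18 − 1) × 0.05. The CV values are assumptions, as the document gives none.

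| Setting | Design effect | Effective n per arm | Power, t on 28 df |
|---|---|---|---|
| Equal homes | 1.209 | 64.3 | 75.4% |
| CV 0.4 (assumed) | 1.250 | 62.1 | 74.0% |
| CV 0.6 (assumed) | 1.302 | 59.7 | 72.3% |

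**The case against.** The strongest reply is that the error is too small to matter. One or two points of power are far less than the uncertainty in an assumed difference of 1.5 and in an SD from an uncontrolled pilot of 30 people. The inputs are printed to one decimal, and an unrounded SD near 3.05 would explain the 65. The loss allowance is also generous: 7.5% covers three months, while the primary outcome is at eight weeks. At a constant rate (an assumption), loss by then is 30% × 8/52 = 4.6%. That leaves 84 × 0.954 = 80.1 per arm, an effective 65.8 per arm and 79.3% power. The planned mixed model also uses all available data from patients who drop out.

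Most of this stands, and it is why the point is minor. It does not make 65 correct. The SD explanation cannot be confirmed from the document, and a reader who uses the printed inputs gets 68. The generous loss allowance narrows the gap but does not quite close it.

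A reader might infer something stronger: that the error in 65 brings power down to anywhere between 72% and 78%, or raises the detectable difference to 1.6 points or more. The document does not support that. The error leaves about 78% and 1.53 points. Anything lower needs a cluster-level t reference, and the article fixes no degrees-of-freedom method; a detailed analysis plan may do so. Figures of 72 to 74% also need a variation in home size that is nowhere given. Nor is multiplying by 1.075 instead of dividing by 0.925 worth raising: 167.7 against 168.6 is less than one patient.

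**Conclusion.** The point holds as a minor arithmetic error. On a two-sided reading, the stated difference, SD, power and significance level require 68 per group, and none of the standard readings tried gives 65 from the printed inputs. The figures 78, 156 and 168 inherit the shortfall. With ICC 0.05, 7.5% loss and 30 equal homes, the planned 168 patients have about 78% power for 1.5 points, roughly two percentage points below the claim. No endpoint, analysis or trial procedure is affected. The figures of 75% and 72 to 74% are useful context on few and unequal clusters, but they rest on further assumptions and are not consequences of this error.

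**What to change.** Choose one of two corrections.

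1. Correct the chain: 68 per group, 82 per group after clustering, and about 174 (unrounded) to 178 (rounded up at each step) in total. This adds 6 to 10 patients.
2. Keep 168 and restate the power as about 78% for a difference of 1.5 points, or 80% for about 1.53 points, on the stated ICC, loss and 30 equal homes. This adds no patients and changes only the text.

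In either case, state that the test is two-sided. If the 65 came from an unrounded SD, print that SD. A separately labelled sensitivity statement could add, for 168 patients, about 75% power with a t reference on 28 degrees of freedom, and about 72 to 74% if home sizes also vary with an assumed CV of 0.4 to 0.6. The cost is a few lines of text and a slightly less favourable power figure.

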### Randomization

Nursing homes will be stratified by size into three blocks to assure approximately equal number of patients in the two trial arms. Block size will be fixed—block 1: 1–5 patients, block 2: 6–9 patients, and block 3: 10 or more patients. Then, nursing homes within each block will be randomly assigned to either the intervention group or the control group. A researcher will perform the randomization procedure independently of the project management team and the nursing homes. The project management team will provide the nursing homes with the randomization and allocation results immediately following this procedure. Specially trained project nurses who are not affiliated with the nursing homes will assess patients’ baseline characteristics before randomization. These assessors will also assess the effect of the intervention via telephone at weeks eight and 12 and will be blinded to the randomization result.

### Control and intervention phases of the study

#### Similar education and training for the staff in CNH and INH—CNH continue practice as usual

Three nurses in each unit in both the INH and CNH will be given a special responsibility in the trial. Before randomization, these nurses will complete a three-hour training on the procedure. Their main task will be to facilitate the interviews for the assessments at baseline, and after 8 and 12 weeks. These nurses will be selected by the leading ward registered nurse based on the following criteria: nurses who work on a nearly full-time basis, have shown interest in professional development and have gained legitimacy with the rest of the staff. Thus, these nurses can be selected among registered nurses, auxiliary nurses, nursing aides or members of other professional groups in the nursing homes.

After randomization, the staff in the INH and the CNH will be offered a two-hour lecture about dementia and NPS. This lecture represents the education-only intervention administered to the staff in the CNH. These staff members will then continue practice as usual for the patients throughout the remainder of the trial.

